### **Events NOT considered to be SAEs are hospitalisations for:**

- routine treatment or monitoring of pre-eclampsia, not associated with any deterioration in condition
- treatment, which was elective or pre-planned, for a pre-existing condition that is unrelated to the indication under study, and did not worsen
- admission to a hospital or other institution for general care, not associated with any deterioration in condition
- treatment on an emergency, outpatient basis for an event not fulfilling any of the definitions of serious given above and not resulting in hospital admission

### **Expected SAEs**

Expected SAEs are those listed in the current Summary of Product Characteristics (SmPC) for Pravastatin. These events do not meet the criteria of SUSAR unless for reason of their severity. For convenience, the

current expected events for Pravastatin are listed in Appendix D. We will however always use the most recently updated Summary of Product Characteristics (SmPC). The BCTU will ensure that any SmPC updates are circulated to all investigators; in addition, up-to-date SmPCs of licensed products are available at <http://emc.medicines.org.uk/>.

Expected SAEs also include, but are not limited to, the following:

- Symptoms and recognised complications of pre-eclampsia. These include exacerbation of hypertension, abnormal renal function, abnormal hepatic function, disseminated intravascular coagulation, cerebrovascular event, eclampsia, left ventricular failure, haemorrhage and pulmonary oedema.
- Symptoms and recognised complications of premature birth. These include seizures, necrotising enterocolitis (NEC), hypoglycaemia, jaundice, bleeding from umbilicus, and congenital anomalies.

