### **Serious Adverse Events (SAEs)**

An SAE is an untoward event which:

- Results in maternal or fetal death
- Immediately threatens the life of mother or baby\*
- Results in a longer than anticipated post-natal maternal stay in hospital
- Results in a persistent or significant disability in the mother
- Results in any congenital anomaly or birth defect in the baby, once delivered, that had not been identified by antenatal ultrasound prior to the onset of pre-eclampsia

\*Life-threatening in the definition of a serious adverse event or serious adverse reaction refers to an event in which the subject was at risk of death at the time of the event. It does not refer to an event which hypothetically might have caused death if it were more severe. Important adverse events/reactions that are not immediately life-threatening or do not result in death or hospitalisation, but may jeopardise the subject or may require intervention to prevent one of the other outcomes listed in the definition above, should also be considered serious.

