### **Suspected unexpected serious adverse reactions (SUSARs)**

A SUSAR is an SAE suspected to be related to a product, which is of a **type or severity** which is NOT consistent with the up-to-date product information (i.e. SmPC).

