#### **7.4. Reporting SUSARs**

SAEs categorised by the local investigator as **both** suspected to be related to the trial drug **and** unexpected are SUSARs, and are subject to expedited reporting.

All SUSARs must be recorded on the SAE Form and faxed to the BCTU on [name] immediately or within 24 hours of the research staff becoming aware of the event. The Chief Investigator (CI) or nominated individual will undertake urgent review of SUSARs within 24 hours of reporting and may request further information immediately from the patient's clinical team. The CI will not overrule the causality, expectedness or seriousness assessment given by the local investigator. If the CI disagrees with the local investigator's assessment, further clarification and discussion should take place to reach a consensus. If a consensus cannot be reached, both the opinion of the local investigator and the CI should be provided in the report to the Medicines and Healthcare and Regulatory Agency (MHRA) and the MREC.

The BCTU will report all SUSARs to the MHRA and the main REC. If the SUSAR resulted in death or was life-threatening this will be done within 7 days of the initial report being received, or within 15 days for any other SUSAR.

If information is incomplete at the time of initial reporting, or the event is ongoing, the BCTU will request follow-up information, including information for categorisation of causality, from the local investigator and will send the follow-up information to the MHRA and main REC within an additional 8 days for fatal or life-threatening SUSARs and as soon as possible for any other events.

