## APPENDIX D: PRAVASTATIN - EXPECTED TOXICITIES

Toxicities/side-effects that have previously occurred and are listed in the pravastatin SMPC do not have to be reported to the MHRA. If the outcome of the side-effect is serious, the SAE form should be completed. Any SAE not described below, i.e. a serious toxicity that is unexpected, and believed to be related to study treatment, will be reported as a SUSAR (see section 7 of the protocol).

Pravastatin has been studied at 40mg in seven randomised double-blind placebo-controlled trials involving over 21,000 patients treated with pravastatin (n = 10764) or placebo (n = 10719). The following adverse drug reactions were reported; none of them occurred at a rate in excess of 0.3% in the pravastatin group compared to the placebo group.

The frequencies of adverse events are ranked according to the following: very common ( $\geq 1/10$ ); common ( $\geq 1/100, < 1/10$ ); uncommon ( $\geq 1/1,000, < 1/100$ ); rare ( $\geq 1/10,000, < 1/1,000$ ); very rare ( $< 1/10,000$ ).

Nervous system disorders: Uncommon: dizziness, headache, sleep disturbance, insomnia

Eye disorders: Uncommon: vision disturbance (including blurred vision and diplopia)

Gastrointestinal disorders: Uncommon: dyspepsia/heartburn, abdominal pain, nausea/vomiting, constipation, diarrhoea, flatulence

Skin and subcutaneous tissue disorders: Uncommon: pruritus, rash, urticaria, scalp/hair abnormality (including alopecia)

Renal and urinary disorders: Uncommon: abnormal urination (including dysuria, frequency, nocturia)

Reproductive system and breast disorders: Uncommon: sexual dysfunction

General disorders: Uncommon: fatigue

Events of special clinical interest:

Skeletal muscle: effects on the skeletal muscle, e.g. musculoskeletal pain including arthralgia, muscle cramps, myalgia, muscle weakness and elevated CK levels have been reported in clinical trials. The rate of myalgia (1.4% pravastatin vs 1.4% placebo) and muscle weakness (0.1% pravastatin vs < 0.1% placebo) and the incidence of CK level  $> 3 \times \text{ULN}$  and  $> 10 \times \text{ULN}$  in CARE, WOSCOPS and LIPID was similar to placebo (1.6% pravastatin vs 1.6% placebo and 1.0% pravastatin vs 1.0% placebo, respectively).

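### Section 7.1 lists congenital anomalies as expected SAEs while the SUSAR definition judges expectedness by the SmPC, so an anomaly judged related to pravastatin could miss expedited reporting

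*Combined protocol and SAP*

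**What the plan says.** Under its SAE definition, section 7.1 counts as serious an event that "Results in any congenital anomaly or birth defect in the baby, once delivered", provided the anomaly had not been seen on ultrasound before pre-eclampsia began.

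Under Expected SAEs, the same section first ties expectedness to the current pravastatin SmPC. It then opens a second list: "Expected SAEs also include, but are not limited to, the following". This covers complications of pre-eclampsia and of premature birth, and the prematurity entries end with "hypoglycaemia, jaundice, bleeding from umbilicus, and congenital anomalies".

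The SUSAR definition that follows has a single reference. A SUSAR is a suspected related SAE whose type or severity is "NOT consistent with the up-to-date product information (i.e. SmPC"). Section 7.3 likewise sends the assessor to the SmPC when recording expectedness. Appendix D directs that "Any SAE not described below, i.e. a serious toxicity that is unexpected, and believed to be related to study treatment" be reported as a SUSAR.

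Section 7.4 sets the operating trigger: SAEs that the local investigator considers both related and "unexpected are SUSARs, and are subject to expedited reporting". Under 7.4 and 7.6 the Chief Investigator may discuss and comment on the local assessment but may not overrule it.

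**The concern.** Expectedness is the switch between expedited and periodic reporting of a related SAE, and the protocol gives two references for it that disagree about congenital anomalies. Whether a suspected drug-related anomaly reaches the regulator in days or in an annual report could depend on which paragraph a site consults.

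This event matters to this trial. Section 2.3.4 explains that statins, pravastatin included, are contraindicated in pregnancy, and the category X definition it quotes refers to fetal abnormality. Section 2.3.4 also calls 32 reported pravastatin exposures too few for reassurance, and section 2.4.1 says the safety of statins in pregnancy is uncertain. Adverse effects on the baby are one of the trial's stated questions (section 2.5).

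**Working it through.** The plan states no figure to reproduce on this point. The check follows one event through each rule: an anomaly found after delivery, not seen on ultrasound before pre-eclampsia began, and judged possibly, probably or definitely related to the trial drug.

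1. *Serious?* Yes, by the SAE definition in 7.1. Related? Yes, by assumption. Section 7.3 then makes it a serious adverse reaction.
2. *Expected?* The rules diverge here:

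| Step | Route A: added list in 7.1, then 7.4 | Route B: SUSAR definition in 7.1, 7.3, Appendix D |
|---|---|---|
| Reference | List of disease and prematurity complications | SmPC, or the Appendix D list drawn from it |
| Anomaly on the list? | Yes, by name | No, in Appendix D as shown |
| Classification | Expected, not a SUSAR | Unexpected, a SUSAR |
| Report to MHRA and main REC | Annual SAE report | 7 days if fatal or life-threatening, otherwise 15 days |
| Trial Office unblinding (6.4) | Not triggered | Triggered |
| Chief Investigator | Review as one of all SAEs (7.6) | Urgent review within 24 hours (7.4) |

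3. *Does any rule settle the conflict?* None states precedence. The added list is not confined to events judged unrelated and is expressly open-ended. The no-overrule provision means that a local decision to call the event expected stands.
4. *What is common to both routes?* The SAE form goes to the trials unit within 24 hours (7.3). The Chief Investigator reviews all SAEs (7.6). The DMEC sees SAEs about every 3 months, blinded but able to unblind (7.3). Deaths go to the DMEC for continuous review (7.5). Table 1 has anomalies recorded at birth and at 6 weeks.
5. *Is the conflict confined to anomalies?* No. Eclampsia, pulmonary oedema and necrotising enterocolitis are also on the added list and absent from Appendix D as shown, so they split in the same way if judged related.

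One calculation needs a limit placed on it. Section 2.4.1 gives 3 VACTERL cases in 550 exposures against a background of 1 in 3,500: 3/550 = 0.545%; 1/3,500 = 0.0286%; ratio 0.545/0.0286, about 19. Section 2.3.4 says that use in the reviewed cases was confined to the first trimester and that the drugs were lovastatin or simvastatin. StAmP gives pravastatin after 24 weeks, to women whose 20-week scan showed no major anomaly (4.2.1). Section 2.3.4 reports no abnormality in the 32 pravastatin exposures. The ratio therefore does not estimate risk in this trial, and the inconsistency does not depend on it.

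**The case against.** The strongest defence is that most of the text points the right way. The SUSAR definition, the instruction at the point of completing the SAE record and Appendix D all lead to the product information. Section 7.4 does not cite the added list. The sentence in 7.1 saying that expected events are not SUSARs unless for their severity is attached to the SmPC-listed events and comes before the added list. The anomaly entry also sits under complications of premature birth, so it can be read as not covering an anomaly attributed to the drug. All of this stands as far as it goes: a reader might infer that a related anomaly is bound to escape expedited reporting, and the documents do not support that. They show only that it could, because 7.4 turns on the word unexpected and 7.1 names anomalies as expected without qualification.

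A reader might also infer that the event would go unreported. It would not, as step 4 of the working shows. A third inference, that the 19-fold ratio sizes the hazard here, fails because of the drugs and the trimester involved.

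A further objection concerns the remedy. If the SmPC alone decides expectedness for every related SAE, then eclampsia or pulmonary oedema judged possibly related becomes a SUSAR. That brings Trial Office unblinding under 6.4, and 6.5 names a suspected unexpected serious adverse reaction among the grounds for stopping treatment. This objection stands, and the amendment must address it. It does not apply to anomalies, which under the SAE definition are identified once the baby is delivered, when treatment has already ended.

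**Conclusion.** The protocol contradicts itself. A newly found congenital anomaly judged related to pravastatin is a SUSAR under the SUSAR definition, 7.3 and Appendix D, and is not one if the added list in 7.1 is applied through 7.4. The consequence is limited to the reporting route: a 7- or 15-day report to the MHRA and REC could become an entry in an annual report, and Trial Office unblinding and urgent Chief Investigator review could fall away with it. Neither the primary analysis nor the sample size is affected.

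The conclusion assumes that the SmPC, like Appendix D as shown, lists no congenital anomaly as an adverse reaction. The SmPC is not in the documents. If it did list one, the two routes would agree for that event, though two references for expectedness would still need reconciling for the other complications.

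**What to change.** Delete congenital anomalies from the expected list in 7.1. In the same amendment, reconcile 7.1, 7.3, 7.4 and Appendix D so that one stated reference decides expectedness for SUSAR reporting. The SUSAR definition already names the SmPC.

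The remaining added complications that Appendix D does not show, such as eclampsia, pulmonary oedema and necrotising enterocolitis, must be reconciled too. Because their classification feeds into unblinding (6.4) and withdrawal of treatment (6.5), those sections should be read against the revised definition and made consistent with it. The clinical rule itself is for the investigators to settle.

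The cost is a protocol amendment and a line of guidance to sites, with possibly a few more expedited reports and Trial Office unblindings. With up to 64 women randomised in equal ratio, about 64/2 = 32 on pravastatin, the added load should be small.

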### **Suspected unexpected serious adverse reactions (SUSARs)**

A SUSAR is an SAE suspected to be related to a product, which is of a **type or severity** which is NOT consistent with the up-to-date product information (i.e. SmPC).

## **7.2. Reporting AEs**

All adverse events, from the first administration of trial treatment until 6 weeks after child-birth, whether observed directly or reported by the patient, will be collected and recorded. Non-serious adverse reactions or events are not required to be reported in an expedited manner, but will be recorded on the daily data collection forms.

## **7.3. Reporting SAEs**

All SAEs must be recorded on the SAE Form and faxed to the BCTU on [name] within 24 hours of the research staff becoming aware of the event. The Principal Investigator (or other nominated clinician) has to assign seriousness, causality and expectedness to the SAE before reporting. All SAEs should be assessed for seriousness, causality and expectedness as though women were prescribed Pravastatin.

For each SAE, the following information will be collected:

- full details in medical terms with a diagnosis, if possible
- its duration (start and end dates; times, if applicable)
- action taken
- outcome
- causality, in the opinion of the investigator\*
- whether the event would be considered expected or unexpected\* (refer to the most recent and relevant Summary of Product Characteristics)

\*Assessment of causality and expectedness must be made by a doctor. If a doctor is unavailable, initial reports without causality and expectedness assessment should be submitted to the BCTU by a healthcare professional within 24 hours, but must be followed up by medical assessment as soon as possible thereafter, ideally within the following 24 hours. An SAE which is assessed as possibly, probably or definitely related to trial treatment is classified as a Serious Adverse Reaction (SAR)

The local investigator and others responsible for patient care should institute any supplementary investigations of SAEs based on their clinical judgement of the likely causative factors and provide further follow-up information as soon as available. If a mother or baby dies, any post-mortem findings must be provided to the BCTU. The BCTU will report all deaths to the DMEC for continuous safety review.

SAEs still present at the end of the trial must be followed up at least until the final outcome is determined, even if it implies that the follow-up continues after the patient finishes the trial treatment and when appropriate until the end of the planned period of follow-up.

The BCTU will report all SAEs to the DMEC approximately 3-monthly. The DMEC will view data blinded to treatment but will be able to review unblinded data if necessary. BCTU will also report all SAEs to the main REC and MHRA annually, and to the Trial Steering Committee 6-monthly. The main REC, MHRA and TSC will only view data blinded to trial treatment. Local Investigators are responsible for reporting SAEs to their host institution, according to local regulations, but they do not need to inform MHRA or main REC as this will be done by the BCTU as detailed above.

#### **7.4. Reporting SUSARs**

SAEs categorised by the local investigator as **both** suspected to be related to the trial drug **and** unexpected are SUSARs, and are subject to expedited reporting.

All SUSARs must be recorded on the SAE Form and faxed to the BCTU on [name] immediately or within 24 hours of the research staff becoming aware of the event. The Chief Investigator (CI) or nominated individual will undertake urgent review of SUSARs within 24 hours of reporting and may request further information immediately from the patient's clinical team. The CI will not overrule the causality, expectedness or seriousness assessment given by the local investigator. If the CI disagrees with the local investigator's assessment, further clarification and discussion should take place to reach a consensus. If a consensus cannot be reached, both the opinion of the local investigator and the CI should be provided in the report to the Medicines and Healthcare and Regulatory Agency (MHRA) and the MREC.

The BCTU will report all SUSARs to the MHRA and the main REC. If the SUSAR resulted in death or was life-threatening this will be done within 7 days of the initial report being received, or within 15 days for any other SUSAR.

If information is incomplete at the time of initial reporting, or the event is ongoing, the BCTU will request follow-up information, including information for categorisation of causality, from the local investigator and will send the follow-up information to the MHRA and main REC within an additional 8 days for fatal or life-threatening SUSARs and as soon as possible for any other events.

#### **7.5. Notification of deaths**

All deaths will be reported to the BCTU on the SAE Form irrespective of whether the death is related to disease progression, the IMP, or an unrelated event. If a mother or baby dies, any post-mortem findings must be provided to the BCTU with the SAE form. The BCTU will report all deaths to the DMEC for continuous safety review.

#### **7.6. Pharmacovigilance responsibilities**

**Local Principal Investigator (or nominated individual in PI's absence):**

- To record **all** AE/Rs that occur in the subjects taking part in the trial. This includes non-serious, serious, expected or unexpected adverse events or reactions.
- Medical judgement in assigning seriousness, expectedness and causality to AEs.

- To fax SAE forms to BCTU within 24 hours of becoming aware, and to provide further follow-up information as soon as available.
- To report SAEs to local committees if required, in line with local arrangements.
- To sign an Investigator's Agreement accepting these responsibilities.

**Chief Investigator (or nominated individual in CI's absence):**

- To assign causality and expected nature of SAEs where it has not been possible to obtain local assessment
- To review all events assessed as SAEs in the opinion of the local investigator
- To review all events assessed as SUSARs in the opinion of the local investigator. In the event of disagreement between local assessment and Chief Investigator with regards to SUSAR status, local assessment will not be over-ruled, but the Chief Investigator may add comments prior to reporting to MHRA.

**Birmingham Clinical Trials Unit:**

- To report SUSARs to MHRA and main REC within required timelines as detailed above
- To prepare annual safety reports to MHRA, main REC and TSC.
- To prepare SAE safety reports for the DMEC at 3-monthly intervals. Data will be presented blinded to treatment, but the DMEC will be able to review unblinded data if necessary.
- To report all fatal SAEs to the DMEC for continuous safety review
- To notify Investigators of SUSARs which compromise patient safety

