**Data Monitoring & Ethics Committee (DMEC):**

- To review (initially at approx 3-monthly intervals) overall safety and morbidity data to identify safety issues which may not be apparent on an individual case basis
- To recommend to the TSC whether the trial should continue unchanged, continue with protocol modifications, or stop.

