### **10.3. Data Monitoring and Ethics Committee: Monitoring Safety**

If pravastatin for pre-eclampsia demonstrates substantial harm to mother or baby, then this may become apparent before the target recruitment has been reached. Alternatively, new evidence might emerge from other sources that statins show substantial benefit or harm to pregnant women and their babies. To protect against this, during the period of recruitment to the trial, interim analyses of safety and morbidity outcomes will be supplied, in strict confidence, to an independent Data Monitoring and Ethics Committee (DMEC) along with updates on results of other related studies, and any other analyses that the DMEC may request. The DMEC will consider safety every 3 months. The DMEC will also be given reports of data quality

at 6 monthly intervals. As this is a pilot study, there is no intention to stop the study early on the grounds of potential efficacy, and thus the DMEC will not be supplied with unblinded results of the main outcome.

The DMEC will advise the chair of the Trial Steering Committee if, in their view, the trial should be stopped on safety grounds, or if protocol modifications are needed.

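### The protocol specifies no expedited notice to the DMEC for a non-fatal SUSAR, so the report can wait up to about three months, by which time most women then on drug will usually have delivered

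*Combined protocol and SAP*

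**What the plan says.** Expedited reporting is set out in section 7.4: "The BCTU will report all SUSARs to the MHRA and the main REC". The clock depends on outcome: if the event led to death or "was life-threatening this will be done within 7 days of the initial report being received, or within 15 days for any other SUSAR". The Chief Investigator reviews each SUSAR within 24 hours. In section 7.6 the Birmingham Clinical Trials Unit (BCTU) also has the duty "To notify Investigators of SUSARs which compromise patient safety", with no time limit.

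The DMEC is served differently. Section 7.3 says "The BCTU will report all SAEs to the DMEC approximately 3-monthly", section 7.6 repeats the interval as a BCTU duty ("To prepare SAE safety reports for the DMEC at 3-monthly intervals"), and section 10.3 says "The DMEC will consider safety every 3 months". The one exception is death: sections 7.3 and 7.5 send all deaths to the DMEC for continuous review, whatever their cause, and the BCTU list in 7.6 has "To report all fatal SAEs to the DMEC for continuous safety review".

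The DMEC's remit in section 7.6 includes the duty "To recommend to the TSC whether the trial should continue unchanged, continue with protocol modifications, or stop". Section 10.3 adds that it advises the TSC chair if the trial should stop on safety grounds.

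**The concern.** A non-fatal SUSAR is an event that an investigator has judged serious, unexpected and possibly, probably or definitely related to trial drug. Section 7 warns that such reactions may occur, because pregnancy could change pravastatin's toxicity in ways nobody has foreseen. Yet no section puts such an event before the DMEC until the next periodic SAE report. The TSC has no faster route: section 7.3 gives it SAEs every six months, and section 7.6 an annual report.

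The ordering is hard to defend on the protocol's own terms. A death unrelated to treatment goes to the DMEC for continuous review, while a life-threatening reaction attributed to the drug waits for the quarterly batch. What is at stake is how soon the independent committee can consider whether women on drug, or about to be randomised, are at risk.

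**Working it through.** The protocol gives no figure for this delay, so there is nothing to reproduce. The check compares the reporting routes, then compares the delay with time on drug.

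**Routes (sections 7.3 to 7.6 and 10.3)**

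| Event | MHRA and main REC | DMEC |
|---|---|---|
| Death, any cause | 7 days if a SUSAR; otherwise annual | Continuous review |
| Life-threatening, non-fatal SUSAR | 7 days | Next report, about 3-monthly |
| Other non-fatal SUSAR | 15 days | Next report, about 3-monthly |
| Other SAE | Annual | Next report, about 3-monthly |

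**Inputs**

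- Reporting cycle: 3 months, taken as 365.25/4 = 91.3 days.
- Duration of pregnancy with pre-eclampsia: 11±5 days (section 8.2). I read this as mean and SD, and apply it to time on drug because section 6.2.2 continues treatment until the pregnancy ends.
- Alternative means: 7.1 to 15.4 days under expectant management (section 2.2).
- Assumptions: the event falls uniformly within a cycle; women on drug are in steady state; there is no data cut-off before each DMEC report (a cut-off would lengthen the wait).

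**Step 1: wait for the next report.** Range 0 to 91.3 days; mean 91.3/2 = 45.7, about 46 days.

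**Step 2: time left on drug for a woman on drug at the event.** Mean residual time = (mean² + SD²)/(2 × mean) = (121 + 25)/22 = 6.6 days.

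**Step 3: chance that she is still on drug at the report, averaged over the cycle.** 6.6/91.3 = 7.3%, so about 93% have delivered. With the section 2.2 means and the same coefficient of variation (5/11, an assumption), mean residual time is mean × (1 + 25/121)/2 = mean × 0.603. That gives 4.3 days (4.7%) for a mean of 7.1, and 9.3 days (10.2%) for a mean of 15.4.

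**Step 4: chance that all k women on drug at the event have delivered.** Let R(t) be the probability that the residual time exceeds t. The chance is the average of (1 − R(t))^k over the cycle, integrated numerically under truncated normal, gamma and lognormal durations. The three agree closely: about 93% for k = 1, 90% for k = 2, 88% for k = 3 and 86% for k = 5. The documents do not say how many women are on drug at once, so k is assumed.

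**Step 5: events late in the cycle.** Mean + 2 SD is 11 + 10 = 21 days, and 21/91.3 = 23% of the cycle lies within 21 days of the next report. A SUSAR in that window can reach the DMEC while some women are still on drug.

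**Step 6: what the existing expedited clock would give.** Across the three distributions, R(7) is 39% to 42% and R(15) is 5% to 7%. At the present mean wait of about 46 days it is about 0.01% or less.

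**Step 7: new randomisations during the wait.** Accrual is not stated. For illustration only, if 64 women were recruited over an assumed 24 to 48 months (64/24 = 2.7 to 64/48 = 1.3 per month), about 2 to 4 would join in 1.5 months and 4 to 8 in 3 months, half of them allocated to pravastatin.

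**The case against.** The strongest reply is that this is a deliberate division of labour. Section 7.6 asks the DMEC to look at accumulated data for problems that single cases would not reveal. Single cases go elsewhere, and quickly: to the Chief Investigator within 24 hours, and to two bodies outside the trial team within 7 or 15 days. The Chief Investigator cannot overrule the local assessment, and any disagreement is sent on with both opinions. Investigators are told of SUSARs that compromise safety, section 6.5 lists a SUSAR among the reasons for withdrawing treatment, and section 6.4 provides a 24-hour code-break.

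All of that stands as description, and nothing in the protocol contradicts itself here. It does not close the gap, because none of these steps informs the DMEC. Nor is the division consistent, since the DMEC already receives individual deaths. Section 10.3 lets the DMEC ask for further analyses, but it cannot ask about an event of which it has not been told.

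Three stronger readings are tempting and are not supported:

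- A reader might infer that every woman then on drug will have delivered before the DMEC hears. That would be roughly true at the mean wait but not across the cycle: about 7% are still on drug on average, and section 6.2.3 expects some deliveries after 28 days.
- A reader might infer that the DMEC is barred from acting sooner. The documents are only silent. The interval is approximate, section 7.6 calls it an initial one, and nothing forbids earlier notice.
- A reader might take a SUSAR to be the main early warning that the trial offers. Deaths go to the DMEC for continuous review, and section 2.4.1 names length of pregnancy after randomisation as information for that committee about harm.

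It is also fair to say that for SUSARs on the 15-day clock, few of the women then on drug (5% to 7%) would still be on it at day 15. The gain there is mainly for women not yet randomised.

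**Conclusion.** The point holds as a gap in routing. The protocol requires no expedited notice to the DMEC for a non-fatal SUSAR, while it requires such notice to the MHRA and main REC and requires continuous DMEC review of deaths. The wait is 0 to about 91 days, mean about 46. About 93% of women on drug at the event will have delivered by the report, or roughly 90% to 95% across the means in section 2.2.

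These percentages rest on a uniform event time, steady state, and the 11±5 days read as mean and SD of time on drug. The number of women randomised during the wait is unknown; the illustrative counts depend wholly on an assumed recruitment period and do not carry the conclusion. The routing gap itself depends on none of these assumptions. It is a design choice that should be improved, not an internal contradiction, and no sample-size or power figure is affected.

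**What to change.** In section 7.4, and in the BCTU list in section 7.6, add wording to this effect:

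> BCTU will send every SUSAR report, and any follow-up to it, to the DMEC at the same time as to the MHRA and main REC. Unblinded allocation will be available to the DMEC if necessary, as in sections 7.3 and 7.6. The DMEC will tell the TSC chair whether an unscheduled review is needed.

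Keep the 3-monthly report for other SAEs.

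This leaves the blinding rule alone: the DMEC sees blinded data by default and may see allocation if it needs to. Sending allocation with every case would change that rule and would need its own justification. Section 6.4 already has possible SUSARs unblinded at the Trial Office with sites kept blind, so allocation could be supplied on request without telling sites.

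The DMEC's longest wait would fall from about 91 days to 7 or 15 days. The cost is a short addition in two places, one extra recipient for a report already being prepared, and an occasional unscheduled DMEC discussion.
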